## Abstract

Introduction: The “paternalistic decision-making model” is no longer well suited to the modern clinical environment, and therefore, shared decision making (SDM) has emerged as a key approach. Although the benefits of SDM have been largely reported, several studies have reported low participation in SDM in coronary artery disease (CAD) patients. The theory of planned behavior (TPB) model is one of the most frequently employed theoretical frameworks for predicting human behaviors. According to the TPB, intention is influenced by attitude, subjective norm, and perceived behavioral control, while behavior is influenced by both intention and perceived behavioral control. Therefore, we propose a mixed methods study based on TPB to investigate the status of Chinese stable coronary artery disease (SCAD) patients’ participation in SDM, understand their experiences of SDM, and explore the factors that influence their participation in SDM. Materials and Methods: An explanatory sequential mixed methods design will be used to explore the study aims, including a quantitative phase, a subsequent qualitative phase, and the final integration study. The quantitative study will use convenient sampling from the Affiliated Hospital of Hangzhou Normal University to conduct a cross-sectional survey (n ≥ 252). The qualitative study will be sampled using the maximum difference sampling method from the quantitative study results, and then the data will be collected through semi-structured interviews (n = 10–20). This study will use descriptive statistics and test hypotheses while considering a *p*-value of <0.05, which will be considered statistically significant. Discussions: The study employs a mixed method approach with an explanatory sequential design, incorporating qualitative and quantitative methods to comprehensively understand the factors influencing SCAD patients’ participation in SDM. Furthermore, these findings can inform the design of future intervention studies and provide healthcare providers with targeted information and communication to help SCAD patients make the most appropriate decisions. Study participants will be recruited using convenience sampling from just one single clinical setting, which may limit the findings’ generalizability. Ethics and Dissemination: This study has been approved by the Ethical Committee of the School of Nursing, Hangzhou Normal University (Approval No.: 2024013). All the participants will sign an informed consent form before participating in the survey. The corresponding results and conclusions will be disseminated in journals and conferences after the completion of the study.

## 1. Introduction

Paternalistic decision making can be defined as a situation in which a physician does not fully comprehend the patient’s needs, interests, and preferences [1]. In such instances, the physician may attempt to influence the patient’s actions and decisions on the grounds that they believe it is in the patient’s best interest to do so. In recent decades, advances in medical technology and the updating of medical devices have led to more options for the diagnosis and treatment of diseases, while patients’ access to medical information has become more diverse, and the awareness of their rights has increased significantly. These have led to major changes in medical decision making. The “paternalistic decision-making model”, which has long been the dominant paradigm in medical practice, is no longer well suited to the modern clinical environment, and therefore, shared decision making (SDM) has emerged as a key approach [2]. SDM facilitates a thorough comprehension of treatment choices and associated risks by involving healthcare professionals and patients, emphasizing the importance of disseminating the best available evidence and acknowledging individuals’ and their families’ needs, values, and experiences when making decisions [3,4]. SDM serves as an intermediary approach, bridging the gap between a completely paternalistic model and an entirely patient-driven one. This method fosters an equitable partnership where both the healthcare provider and the patient jointly assume responsibility for making medical decisions [5].

Cardiovascular disease (CVD) represents a significant contributor to mortality, with deaths attributable to CVD representing an increasingly critical concern for global health [6]. As the Global Burden of Disease study indicated, in 2022 alone, CVD caused an estimated 19.8 million deaths worldwide [7]. In China, the number of people suffering from cardiovascular diseases has reached 330 million, and the mortality rate accounts for about 40% of the national mortality rate, of which coronary artery disease (CAD) accounts for 11.39 million, which is the main cause of the death and disability of Chinese residents [8]. Stable coronary artery disease (SCAD) is the most common type of CAD.

Patients with SCAD frequently present with symptoms that impair their quality of life. Common treatment options include optimal medication therapy (OMT) and coronary revascularization therapy [9]. It has been demonstrated that the range of treatment options for SCAD is, in the majority of cases, comparable [10]. In other words, there was no significant difference between the two in terms of long-term symptom relief or reduced risk of heart attack or death. Furthermore, the decision regarding the most appropriate course of treatment is often a matter of personal preference, with different patients requiring and desiring different forms of treatment. SDM not only improves treatment adherence and health outcomes but also directly impacts the patient experience, healthcare satisfaction, and quality of life (QoL) [11]. Multiple cardiovascular guidelines recommend shared decision making for SCAD patients who are capable of autonomous decision making [12,13,14]. Although the benefits of SDM have been largely reported [15], several studies have reported low levels of participation in SDM in CAD patients [12,16,17]. One study revealed that merely 10% of the patients undergoing percutaneous coronary intervention (PCI) are informed of alternative options, only 19% are apprised of potential drawbacks, and just 16% are consulted about their treatment preferences [12]. In the Chinese context, there is a lack of evidence on the factors influencing the participation of SCAD patients in SDM.

The planned behavior theory (TPB) model is often used as a theoretical framework to predict human behavior. The theory posits that observing human behaviors involves a rational decision-making process and asserts that intention dictates behavior. Attitude, perceived behavioral control, and subjective norms have been documented as positively influencing behavior via intention [17]. TPB has been widely used to explain the behavioral intentions and behaviors of various diseases and populations, including physical activity [18], smoking behavior [19], dietary behaviors [20], contraceptive decisions [21], and breastfeeding decision making [22]. However, the factors that comprise the TPB domains among SCAD patients’ participation in SDM are unclear.

Therefore, we propose a mixed methods study based on TPB to investigate the current status of Chinese SCAD patients’ participation in SDM, understand their experiences of SDM, and explore the factors that influence their participation in SDM. Our greater goal is to provide important information and references for designing specific interventions and scaling up SDM in the future.

## 2. Materials and Methods

### 2.1. Research Questions

The objectives of the study are as follows: What is the current status of Chinese SCAD patient’s participation in SDM?

What are the experiences of Chinese SCAD patient’s participation in SDM?

What are the factors influencing Chinese SCAD patients’ participation in SDM?

### 2.2. Theoretical Framework

The theory of planned behavior (TBP) framework was adopted in this study (Figure 1). According to the TPB, intention is influenced by attitude, subjective norm, and perceived behavioral control, while behavior is influenced by both intention and perceived behavioral control [23]. Attitude is a comprehensive assessment of performing a certain behavior. In this study are views on the benefits, disadvantages, and outcomes of participating in SDM behavior.

Subjective norm refers to the social pressure exerted by significant others for someone to engage in a particular behavior and their level of support for that behavior. In this study, it was defined as the degree to which SCAD patients felt the pressure of their significant other and the support they provided when deciding whether to engage in SDM behavior.

Perceived behavioral control measures how a person perceives the ease or difficulty in performing a behavior. Perceived behavioral control increases with individuals’ perceptions of having greater resources and opportunities available to them, along with fewer perceived obstacles. In this study, it is defined as the resources, opportunities, and obstacles that SCAD patients perceive when they participate in SDM behavior.

### 2.3. Design

An explanatory sequential mixed methods design will be used to explore the study aims, including a quantitative phase, a subsequent qualitative phase, and the final integration study (Figure 2). In the quantitative phase of the study, quantitative data on the status of participation in SDM among SCAD patients and the factors influencing it will be collected in large quantities through a cross-sectional study. In the qualitative phase of the study, semi-structured interviews with SCAD patients representing the quantitative results will be conducted through a descriptive qualitative study to deeply explore their subjective feelings and experiences of participating in SDM. Thematic analysis will be used to explore the factors influencing their participation in SDM, which further supplemented the quantitative study. Finally, the results collected in the quantitative and qualitative phases will be integrated, and the statistics-by-themes and side-by-side comparisons will be used in a joint display.

### 2.4. Stage 1: Quantitative Study

#### 2.4.1. Sample

A convenience sampling method will be used to recruit participants. The study included 14 demographic and clinical characteristics and seven dimensions corresponding to five formative scales, with a total of 21 variables (Table 1). According to the sample estimation algorithm proposed by Kendall [24], the sample size is 10–20 times the number of variables, and the minimum sample size of this quantitative survey is 210. Moreover, considering 20% of the lost follow-up rate and invalid questionnaires, the final minimum sample size for the study is 252.

The inclusion criteria are as follows: (1) meets the diagnostic criteria of SCAD in the Guidelines for Diagnosis and Treatment of Stable Coronary Heart Disease [25]; (2) ≥18 years old; (3) signed informed consent.

The exclusion criteria are as follows: (1) patients with emergency admissions; (2) patients fully delegated to the family decision-maker; (3) patients with communication disorders; (4) diagnosed with mental illnesses; (5) pregnant patients; (6) patients with severe cardiac, liver, or renal dysfunction or critical illness.

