#### 2.4.2. Study Setting and Data Collection

The study will be conducted at the Affiliated Hospital of Hangzhou Normal University in Hangzhou, Zhejiang Province, China.

Before the questionnaire survey, team members will receive unified training to master the purpose, method, content, and process of the questionnaire survey. When answering questions from patients, unified guidance language should be used to ensure the authenticity of answers and the reliability of data. With the support and cooperation of hospital staff and the consent of SCAD patients, investigators will require the participants to sign informed consent forms and provide their telephone numbers through which they can be contacted for the next stage. We will be preparing small gifts for patients to stimulate their enthusiasm to participate in the survey.

Data collection stage: One or two days before discharge, the researchers and participants will conduct face-to-face paper-and-pencil surveys to fill out questionnaires. The questionnaire survey will take about 10–15 min. For elderly patients with low educational levels, the researchers will clearly explain the contents of each survey and then ask the offspring of the patients to fill in the questionnaires. The questionnaires will be issued on the spot, and the questionnaires will be collected on the spot and checked in time to ensure the completeness and effectiveness of data collection.

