### 3.2. Limitations

Firstly, our study participants will be recruited using convenience sampling from just one clinical setting. The single setting and the sampling methodology are non-probabilistic, limiting the findings’ generalizability. Secondly, for the elderly with lower levels of education, there is a possibility that they may not be able to comprehend the content of the questionnaires and interview outlines, which could potentially lead to communication difficulties. It is incumbent upon the researcher to elucidate the questionnaire and interview outline to the elderly in simple and clear statements. This may require a greater investment of time and energy on the part of the patient, which could potentially impede the research process.

TPB also has some limitations that should be mentioned. Firstly, TPB assumes that individuals make decisions based on the rational assessments of available information. In reality, however, people often make decisions based on past behavior and habits, which are not fully captured by the theory [39]. This may lead to overestimating the predictive power of attitudes, subjective norms, and perceived behavioral control in some situations. Secondly, TPB assumes that individuals have a degree of control over their behavior. However, in some cases, people may have limited control due to factors such as their medical condition, mental health problems, or environmental constraints. When patients lack control over their behavior, TPB’s predictive power is reduced because intentions may not be translated into action [39].

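### Convenience sampling leaves open which eligible inpatients are approached, so the estimated level of SDM participation may be biased even for this hospital; consecutive sampling at the existing survey point would be a cheap improvement

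*Protocol article*

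**What the plan says.** - Sampling (section 2.4.1): "A convenience sampling method will be used to recruit participants". The abstract also names convenience sampling.
- Aim (section 2.1): the first question is "What is the current status of Chinese SCAD patient’s participation in SDM". Section 2.4.3 measures participation with the SDM-Q-9, rescaled to 0–100 and cut into low (0–33), medium (34–66) and high (67 and above).
- Survey point (section 2.4.2): "One or two days before discharge, the researchers and participants will conduct face-to-face paper-and-pencil surveys to fill out questionnaires". There is one hospital, and a questionnaire takes 10–15 minutes.
- Contact (section 2.4.2): "With the support and cooperation of hospital staff and the consent of SCAD patients", the investigators obtain signed consent and a telephone number. A small gift is offered.
- Limitation (section 3.2): "The single setting and the sampling methodology are non-probabilistic". The consequence drawn there is reduced generalizability.
- Size (section 2.4.1): at least 210 patients, raised to 252 for losses and invalid questionnaires.

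**The concern.** A level depends directly on who enters the sample. Convenience sampling fixes neither the order nor the completeness with which eligible patients are approached. If ease of approach is related to how much a patient takes part in decisions, the low, medium and high shares are shifted. A larger sample does not correct this, because it reduces only the random error.

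Such a relation is plausible. The survey is a face-to-face session with researchers and asks for a telephone number for later contact, and patients who engage readily with that may also engage more in decisions. The article offers no evidence for the relation or its direction.

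At stake is the answer to the first research question, which the authors intend to share with health administration organizations (section 3.3). The Spearman correlations and the logistic regression are less directly exposed, though not immune.

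**Working it through.** **1. The plan's own figure.** 21 variables × 10 = 210, and 210 × 1.20 = 252. Both reproduce. The calculation below uses 210, the number required before the allowance.

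**2. Sampling error.** The 95% half-width of a share p is h = 1.96 × √(p(1−p)/n). The article gives no expected share, so p is an assumption. With p = 0.30 and n = 210, h = 1.96 × √(0.30 × 0.70/210) = 0.062, or ±6.2 points. It is ±4.1 points at p = 0.10, ±5.4 at 0.20 and ±6.8 at 0.50.

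**3. Shift from unequal inclusion.** Let high-level patients be k times as likely as others to enter the sample, that is, to be approached and to agree. The observed share is kp/(kp + 1 − p). The value of k is also an assumption. With p = 0.30:

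| k | Observed share | Shift (points) | Beyond ±6.2? |
|---|---|---|---|
| 1.25 | 0.375/1.075 = 34.9% | +4.9 | No |
| 1.5 | 0.45/1.15 = 39.1% | +9.1 | Yes |
| 2 | 0.60/1.30 = 46.2% | +16.2 | Yes |

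The direction is open. With k = 1/1.5, kp = 0.20, and the observed share is 0.20/0.90 = 22.2%, a shift of −7.8 points.

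**4. Threshold.** The upward shift equals h when k = [(p + h)/(1 − p − h)] ÷ [p/(1 − p)].
- p = 0.30: (0.362/0.638) ÷ (0.30/0.70) = 1.32
- p = 0.10: (0.1406/0.8594) ÷ (0.10/0.90) = 1.47
- p = 0.20: (0.2541/0.7459) ÷ (0.20/0.80) = 1.36
- p = 0.50: (0.5676/0.4324) ÷ 1 = 1.31

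**5. Cross-check on the mean 0–100 score.** Bias = (1 − f) × D, where f is the share of eligible patients surveyed and D is the difference in mean between surveyed and non-surveyed patients. The half-width is 1.96 × SD/√210, which gives 2.03, 2.71 and 3.38 points for assumed SDs of 15, 20 and 25. Bias equals the half-width at D = half-width/(1 − f).
- f = 0.5: D = 4.1, 5.4 and 6.8 points
- f = 0.9: D = 20.3, 27.1 and 33.8 points

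For example, f = 0.5 and D = 10 give a bias of 0.5 × 10 = 5.0 points against a half-width of 2.7 (SD 20). That is 5.0/1.38 = 3.62 standard errors, and a nominal 95% interval would then cover the true mean about 5% of the time. With f = 0.9, or with D = 2 and f = 0.5 (bias 1.0), the bias stays below sampling error.

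**6. What consecutive approach would change.** Both k and (1 − f) combine being approached with agreeing. Consecutive approach acts only on the first. The article does not show how much of any shift belongs to each.

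**The case against.** The strongest reply is that the authors have disclosed the matter. The abstract and section 3.2 name convenience sampling, and section 3.2 lists the sampling method alongside the single setting, so its warning need not be read as applying only to other hospitals. That is fair, and this is not a hidden error. But the section does not say that the level may be distorted among this hospital's own eligible patients, and disclosure does not remove an avoidable bias.

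Other objections stand and limit the point:

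- The values of p, k, f, D and SD are all assumed, and at k = 1.25 the shift lies inside the sampling error.
- An upward direction is not established. Patients who delegate decisions fully to their family are excluded under any sampling method.
- Consecutive approach leaves refusal untouched, and willingness to talk to researchers may act mainly through refusal.
- The article gives no patient volume or team size, so full daily coverage cannot be assumed.

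A reader might infer two stronger points that the article does not support. The first is that hospital staff choose who is surveyed. Section 2.4.2 mentions staff cooperation in connection with consent and contact details, and it does not say who selects patients. The second is that biased shares would set the strata for choosing interviewees. The levels are fixed by the SDM-Q-9 cut-offs, and section 2.5.1 selects for maximum difference across several characteristics. At most, the sample affects how many candidates each level holds. Nor is it a fault that a condensed article mentions no screening log.

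**Conclusion.** The point holds as a design improvement. Convenience sampling is stated as the method, so this is not a detail left to a fuller document, and it is a weak choice for a question about a level when every survey already takes place at one point in the stay. Bias in the low, medium and high shares is possible, but its size and direction cannot be derived from the article.

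In the hypothetical with 30% truly at the high level and n = 210, selection outweighs the ±6.2-point sampling error only if high-level patients are more than about 1.3 times as likely to enter the sample. For assumed shares from 10% to 50%, that threshold runs from 1.47 down to 1.31. The article does not support saying that the bias will exceed the sampling error, only that a moderate difference in inclusion would be enough.

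**What to change.** In section 2.4.1, replace convenience sampling by consecutive sampling. Approach every eligible patient who reaches the pre-discharge survey point until the target is met. If the team cannot cover every day, approach all eligible patients present at that point on survey days fixed in advance. The second option still misses patients whose short pre-discharge window falls between survey days, but the calendar then decides who is missed and convenience does not.

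Report the numbers eligible, approached, refused and surveyed, with age and sex, so that the remaining selection can be judged. In section 3.2, add that the level estimate may be affected by selection within the hospital as well as limited in its generalizability.

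The cost is a short log and possibly slower recruitment. The sample size does not change. Refusal and the single-site limit remain.

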#### 2.4.3. Instruments

Data collection will be performed by using the following instruments:(1)General information questionnaire: Demographic and clinical characteristic data will be obtained by the general information questionnaire. Demographic characteristics will include age, sex, BMI, ethnicity, marital status, education level, average annual household income, place of residence, working conditions, medical payment method, drinking status, and smoking status. Clinical characteristics will include the duration of illness, the first time to be hospitalized for SCAD or not, the severity of angina, stent implantation or not, and the number of diseased coronary arteries.(2)Questionnaire for measuring patient views of involvement in myocardial infarction care [26]: This questionnaire was developed by Judith E, and translated by H. Shen [27]. Patient attitudes towards SDM will be measured by the patient involvement section of this scale, which consists of 6 items. The responses to each item are scored from 1 (Don’t agree at all) to 4 (Agree completely) with the total scores ranging from 6 to 24 points. A higher score indicates a more positive attitude towards SDM on the part of the patient. Cronbach’s α for the subscale is 0.82, indicating good internal consistency reliability.(3)Decision Self-Efficacy Scale (DSES) [28]: DSES was developed by Bunn et al., and translated by S.T. Wang et al. [29]. Decision self-efficacy is the “self-confidence or belief in one’s abilities in SDM”, and we will use DSES to assess the self-efficacy of participants towards SDM. The response options will be measured on the 5-point Likert scale (0 = not at all confident to 4 = very confident). On the advice of the original author, the total self-efficacy score is obtained by summing the 11 items and then multiplying them by 11/25. The total score ranges from 0 (not confident) to 100 (extremely confident). DESE demonstrated excellent reliability in the original study (Cronbach’s α = 0.899). The English version of DSES was translated into Chinese, back-translated, and cross-culturally adapted according to Brisin’s principles. The Chinese version of DSES consisted of 11 items. The content validity index of the Chinese version scale was 0.966. The Cronbach’s α coefficient was 0.918. The correlation coefficients between the scores of each item and the total score were 0.627–0.796 (all *p* < 0.01).(4)The Autonomy Preference Index (API) [30]: API was developed by Ende, and translated by Kim et al. [31]. The intention was assessed by 6 items using responses on the 5-point Likert scale (1 = “strongly disagree” to 5 = “strongly agree”). Because scoring for these items is reversed, a lower score indicates a greater intention. The internal consistency reliability of the subscale was excellent (Cronbach’s α = 0.82), and the test–retest reliability was 0.84.(5)The 9-item Shared Decision-Making Questionnaire (SDM-Q-9) [32]: SDM-Q-9 was developed by Kriston, and translated by B.H. Luo et al. [33]. The English version of SDM-Q-9 was translated into Chinese, back-translated, and cross-culturally adapted according to Brisin’s principles. The degree of the patient’s actual participation in SDM during treatment will be assessed by 9 items using answers on the 6-point Likert questionnaire ranging from 1 to 6 (“completely disagree” to “completely agree”). The SDM-Q-9 showed excellent validity and high acceptance, and internal consistency yielded a Cronbach’s α of 0.938 in the test sample. The initial author suggested that the original score × 20/9 be converted to 0–100 points for easy comparison. The total scores of 0–33, 34–66, and 67 and above indicated low, medium, and high levels of patient participation in shared decision making, respectively. Higher scores indicate a greater degree of patient participation in SDM.(6)The Multidimensional Scale of Perceived Social Support [34]: MSPSS was developed by Zimet, and translated by Kee-Lee Chou [35]. Perceived social support was measured with the MSPSS. The scale consists of 12 items (Cronbach’s α = 0.89) with answers ranging from “Completely disagree” to “Completely agree” (1 to 7). The measure assesses social support received from three subscales (4 items each)—friend subscales (Cronbach’s α = 0.95), family subscales (Cronbach’s α = 0.92), and significant other subscales (Cronbach’s α = 0.91). The general scores were calculated by adding the 12 items together (ranging from 12 to 84). A higher total score indicates higher levels of social support for patients.

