**Figure 3 healthcare-12-01883-f003:**
[figure not shown]
Gantt chart for this mixed method study.

**Table 1 healthcare-12-01883-t001:** Statistical test information table.

Statistical Test Information Table			
Num	Tests	Variables	Type of Information
1	descriptive statistics	demographic and clinical characteristics, participation in SDM, patient attitudes, decision self-efficacy, intention, and social support	Frequency, percentage; Mean ± SD or M (P_25_, P_75_) (normality or not)
2	monofactor analysis	sex, BMI, ethnicity, place of residence, working conditions, medical payment method, stent implantation or not, and the first time to be hospitalized for SCAD or not	Mann–Whitney U-tests
		age, marital status, education level, average annual household income, drinking status, smoking status, duration of illness, severity of angina, and number of diseased coronary arteries	multi-sample rank-sum tests
3	multiple logistic regression analyses	Variables that are statistically significant after monofactor analysis	independent variables
		participation in SDM	dependent variable
4	Spearman correlation analysis	participation in SDM (Single dimension)	
		patient attitudes (Single dimension)	
		decision self-efficacy (Single dimension)	
		intention (Single dimension)	
		social support (friends support, family support, and significant other support)	

Demographic and clinical characteristics: sex, BMI, ethnicity, place of residence, working conditions, medical payment method, stent implantation or not, and the first time to be hospitalized for SCAD or not; age, marital status, education level, average annual household income, drinking status, smoking status, duration of illness, severity of angina, and number of diseased coronary arteries.

**Table 2 healthcare-12-01883-t002:** Semi-structured Interview Outline.

Opening remarks	I appreciate your interest in this study. I will ask you some questions about your involvement in SDM during this hospitalization. Your responses will be recorded, but your identity will remain confidential.	

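### The minimum sample of 252 rests on a count of 14 characteristics where the protocol lists 17, and on adding 20% where a 20% loss requires dividing by 0.8

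*Protocol article*

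**What the plan says.** The sample size of the quantitative stage is justified in section 2.4.1 of the protocol article by a rule of thumb of 10 to 20 participants per variable. The variable count is given as follows: "The study included 14 demographic and clinical characteristics and seven dimensions corresponding to five formative scales, with a total of 21 variables", with a reference to Table 1. The lower end of the range is used, giving 210. The allowance for loss is then applied: "considering 20% of the lost follow-up rate and invalid questionnaires, the final minimum sample size for the study is 252". The abstract carries the result forward as a "cross-sectional survey (n ≥ 252)".

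The characteristics themselves are listed in two places.

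- Section 2.4.3, item (1), gives the demographic ones as "age, sex, BMI, ethnicity, marital status, education level, average annual household income, place of residence, working conditions, medical payment method, drinking status, and smoking status". The clinical ones are the duration of illness and then "the first time to be hospitalized for SCAD or not, the severity of angina, stent implantation or not, and the number of diseased coronary arteries".
- Table 1 divides the characteristics by the test to be used. The Mann–Whitney row begins with sex and BMI and ends with stent implantation and first hospitalization. The multi-sample rank-sum row reads "age, marital status, education level, average annual household income, drinking status, smoking status, duration of illness, severity of angina" and closes with the number of diseased coronary arteries. The footnote to Table 1 repeats both lists.

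**The concern.** Two separate steps in the calculation look wrong. First, the number of characteristics used in the calculation does not match either list of characteristics, including the table that the section names as its source. Second, the loss allowance was added as 20% of the required number, although it is described as a rate of loss and invalid questionnaires. A rate of loss applies to those recruited, so the recruited number has to be the required number divided by one minus that rate.

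This rule is the only justification given for the size of the survey, and the plan already works at the lowest end of its 10–20 range. There is therefore no slack to absorb either error. A team that stops at the stated minimum would not have what section 2.4.1 claims, namely at least 10 usable questionnaires per variable after 20% loss.

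**Working it through.** **Inputs**

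- Characteristics as stated: 14 (section 2.4.1).
- Characteristics as listed in section 2.4.3: 12 demographic + 5 clinical = 17.
- Characteristics as listed in Table 1: 8 (Mann–Whitney) + 9 (multi-sample rank-sum) = 17. These are the same 17 items as in section 2.4.3.
- Scale dimensions: 7. Table 1 confirms this: participation, attitudes, self-efficacy and intention count one each, and social support counts three.
- Participants per variable: 10, the lower bound of the stated range (section 2.4.1).
- Loss and invalid questionnaires: 20% (section 2.4.1).

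**Reproducing the plan's figure**

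(14 + 7) × 10 = 210, and 210 × 1.2 = 252. This matches exactly. Dividing instead gives 210/0.8 = 262.5, rounded up to 263, which does not match. The plan therefore multiplied by 1.2.

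**What 252 delivers at 20% loss**

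252 × 0.8 = 201.6, so about 201 usable questionnaires.

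- Per variable on the stated count: 201.6/21 = 9.6.
- Per variable on the listed count: 201.6/24 = 8.4.

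**What loss 252 can bear**

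- To leave 210: (252 − 210)/252 = 16.7%.
- To leave 240: (252 − 240)/252 = 4.8%.

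**Corrected figures**

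| Reading | Usable minimum | × 1.2 | ÷ 0.8 |
|---|---|---|---|
| 21 variables, as stated | 210 | 252 | 263 |
| 23 variables (outcome dimension not counted) | 230 | 276 | 288 |
| 24 variables, as listed | 240 | 288 | 300 |

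Every corrected cell exceeds 252. Correcting only the count gives 288 with the plan's own multiplier, and correcting only the loss step gives 263. Correcting both gives 300, a difference of 300 − 252 = 48, and 48/252 = 19%.

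**The case against.** The strongest reply has four parts.

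**Only the count contradicts the document.** The plan nowhere says that it divides by 0.8, and multiplying by 1.2 is a common, if weaker, convention. On that view the count-only correction is 288, and the loss step on its own is worth just 11 participants (263 against 252). This is fair as to weight: the count is the larger error. It does not rescue the figure, because 252 is 36 short of 288 even under the plan's own multiplier, and because at the stated 20% loss 252 does not leave 210.

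**252 is a floor, and the loss may be smaller.** The survey is a single contact, with questionnaires collected and checked on the spot, so over-recruitment or a loss below 20% could close the gap. Both are possible. However, nothing commits the team to recruit beyond 252, and the 20% is the plan's own assumption. With 24 variables the floor holds only if loss stays at or below 4.8%.

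**The regression may not be short.** As Table 1 is written, only the 17 characteristics go through single-factor screening, so at most 17 variables are candidates for the logistic regression, and 201/17 = 11.8 per candidate. This stands as a limit on the consequence. The shortfall is against the rule as section 2.4.1 applies it, to all variables including the scale dimensions. Moreover, the rule involves no significance level, power or effect size, so no loss of power can be calculated from it.

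**The document does not show how 14 arose.** It may be a miscount, or three characteristics may have been added later. That is true, and the authors must settle it. As the text stands, however, both lists give 17 and none gives 14.

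**Conclusion.** The concern holds. The stated minimum is wrong as written. Section 2.4.1 counts 14 characteristics while its cited table and section 2.4.3 both list 17, so the 10-per-variable minimum is 240 rather than 210. The loss step then leaves about 201 usable questionnaires, below either figure. The corrected recruitment minimum is 300, with 263 to 288 under partial corrections or if the outcome dimension is left out of the count.

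This rests on the plan's own terms: 10 participants per variable, all listed characteristics and scale dimensions counted, and 20% of recruited questionnaires unusable. The count error carries most of the weight. What fails is the stated justification for the sample size; an effect on power or on error rates has not been shown and cannot be derived from this rule.

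**What to change.** Reconcile section 2.4.1 with section 2.4.3 and Table 1, giving 17 + 7 = 24 variables and a usable minimum of 240. Then take one of two routes.

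1. **Raise recruitment.** Set the minimum at 240/0.8 = 300 in section 2.4.1 and the abstract. The cost is 48 more participants.
2. **Keep 252.** State that about 201 usable questionnaires, or 8.4 per variable, are expected at 20% loss, and remove the claim that the 10-per-variable minimum is met. The cost is a text edit and a slightly less favourable stated ratio.

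If the authors find that fewer than 17 characteristics are meant to be counted, they should say which ones are left out and why, correct the lists, and recompute with division by 0.8.

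In the same edit, describe the 20% as invalid or incomplete questionnaires. The survey is a single contact before discharge, so loss to follow-up does not apply to it. This is a wording change and does not alter the number.
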